##### Use and functioning of interagency teams (agencies nested within counties)

To examine the activities and functioning of interagency teams, we integrated the NCJTP Relationship Assessment Inventory [38] with additional items based on the goals and priorities of Stepping Up. This integrated scale contains 18 items such as “we share general information about populations in need of treatment services” (0 = no, 1 = yes) with one point assigned for each collaborative activity across the other 3 agencies. The total score (up to 54) reflects joint activities among agencies.

##### Common goals and mission across agencies (agencies nested within counties)

The primary measure (an adapted NCJTP Goals/Mission scale) [38] assesses each respondent’s perception of the degree to which their agency goals and overall county goals align. Respondents are given a list of goals (e.g., public safety/protection, provide mental health services) and are asked to rank them according to (1) their agency’s priorities and (2) county priorities. A kappa score reflects the degree of consistency between the two lists. The secondary measure, a county-level measure, will be agreement (kappa) among respondents within counties on ratings of the importance of providing mental health treatment services for justice-involved individuals in jail and in the community (separately) on a scale of 1 (unimportant) to 10 (important).

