### Power analyses

The expected sample (475 paired counties, up to 4 respondents per county, resulting sample size of ~ 3800) and the response rate of 50% gives an expected sample of 1900 respondents. Given that anywhere from 0 to 4 respondents may complete the survey in any given county, with a 50% overall response rate, we anticipate that 712 counties will have at least one respondent who completes the survey. We used a conservative (higher than expected) intraclass correlation coefficient of 0.1 for addressing clustering of agencies within counties.

For county-level analysis, an effect size of 0.2, power of 0.8, confidence level of 95%, and statistical significance level of 0.05 were used to calculate the minimum sample size. Repeated measures analysis required a minimum total sample size of 304 counties. For logistic regression and other nonlinear predictive models, depending on the type and quantity of variables used in the model, the minimum total sample size required varied between 156 and 489 counties. With attrition, our calculations showed a power of 0.9 and more for most county-level analyses.

For agency-level analysis, a conservative agency-level effect size estimate (*d* = 0.1), a power of 0.8, confidence level of 95%, and significance level of 0.05 were used to calculate the minimum required sample size. Repeated measures analysis comparing respondents from Stepping Up and comparison counties resulted in a minimum sample size of 524 respondents. When comparing the response measures, measured at the agency level, over time, a minimum sample size of 1200 respondents is required. For predictive logistic regression and other nonlinear predictive models, the minimum sample size varied between 673 and 1100 respondents. Given the larger sample size of this study, our calculations showed a power higher than 0.9 for agency-level analyses.

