##### Secondary

We will test the hypothesis that Stepping Up counties will show faster rate of improvement in the *use/functioning of interagency teams* (i.e., total scores on the integrated NCJTP Relationship Assessment Inventory-IOR measure) than control counties using the same statistical techniques. We will test the hypothesis that Stepping Up counties will show faster rate of improvement in *common goals and mission across agencies* (i.e., agreement between perceived agency and county priorities) than comparison counties using GLMM or GEE. We will conduct similar analyses of agreement among respondents within each county on the importance of mental health treatment for justice-involved individuals. We will test the hypothesis that Stepping Up counties will show faster rate of improvement in *system integration* (score of 6 or more on the Relationship Assessment Inventory score) using GEE. Separate secondary analysis will compare rates of change in the use of the same screening and assessment instruments by multiple agencies in Stepping Up and comparison counties.

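### The county-level kappa on a single importance rating carries no information on agreement; the kappa for the ranked goals should be given an order-sensitive form

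*Protocol article*

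**What the plan says.** The section on common goals and mission across agencies defines two measures.

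- **Primary measure.** Respondents get a list of goals and "are asked to rank them according to (1) their agency’s priorities and (2) county priorities". Then: "A kappa score reflects the degree of consistency between the two lists". Neither the number of goals nor the type of kappa is given.
- **Secondary measure.** "The secondary measure, a county-level measure, will be agreement (kappa) among respondents within counties on ratings of the importance" of mental health treatment for justice-involved people, rated "in jail and in the community (separately) on a scale of 1 (unimportant) to 10 (important". The introduction to Measures explains that a county-level measure yields one value per county, and Table 3 lists this agreement measure at all three waves.

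On the number of raters, Power analyses says: "Given that anywhere from 0 to 4 respondents may complete the survey in any given county".

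On use, the secondary part of Aim 1a says: "We will conduct similar analyses of agreement among respondents within each county on the importance of mental health treatment for justice-involved individuals". The analyses it resembles compare rates of change between Stepping Up and comparison counties. The secondary part of Aim 1b then uses scores from the mechanism measures, common goals among them, as mediators.

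**The concern.** Kappa compares observed agreement with the agreement expected from how often each category is used. It needs several rated items to separate the two. Here a county supplies one item per setting, so observed and expected agreement come from the same two to four numbers. If the index cannot move when answers move closer together, comparing its slopes between groups tests nothing about shared goals. Any movement it does show comes from something else, namely how many people replied.

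The ranked-goals measure raises a milder question. Kappa without weights counts only exact rank matches and ignores how far apart two ranks are. For rankings, that distance is most of what alignment means.

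**Working it through.** The article reports no kappa value, so there is no figure to reproduce.

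**A. One rating per respondent (secondary measure)**

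Inputs: one item per setting (the settings are handled separately), 10 categories, and n = 2, 3 or 4 respondents (kappa needs at least 2).

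Fleiss' kappa. Let S be the sum of squared category counts for the item.

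- Observed agreement: P = (S - n) / (n(n - 1))
- Expected agreement: Pe = S / n²
- P - Pe = (S - n²) / (n²(n - 1)) and 1 - Pe = (n² - S) / n²
- Kappa = (P - Pe) / (1 - Pe) = -1/(n - 1). S cancels. If all agree, S = n² and kappa is 0/0.

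Two examples with n = 4:

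- Ratings 9, 9, 9, 10: S = 10, P = 6/12 = 0.500, Pe = 10/16 = 0.625, kappa = -0.125/0.375 = -0.333.
- Ratings 1, 4, 7, 10: S = 4, P = 0, Pe = 4/16 = 0.250, kappa = -0.250/0.750 = -0.333.

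Enumerating every possible set of 1-10 answers confirms this:

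| Respondents | Patterns | Kappa when not unanimous | Unanimous (0/0) |
|---|---|---|---|
| 2 | 100 | -1.000 (90 patterns) | 10 |
| 3 | 1,000 | -0.500 (990) | 10 |
| 4 | 10,000 | -0.333 (9,990) | 10 |

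Cohen's kappa, two respondents. Each person's marginal sits on one category. If they differ, observed and expected disagreement are equal under any weights, so kappa is 0. If they agree, it is 0/0. Enumeration gives 0 in 90 of 100 patterns and undefined in 10, whether unweighted, linear or quadratic.

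What Fleiss' kappa would then pick up is the response count. As an illustration, assume independent responses, ignore unanimous counties, and keep counties with at least two respondents:

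- 60% response: probabilities for 2, 3 and 4 respondents are 0.3456, 0.3456 and 0.1296, so mean kappa = -(0.3456 + 0.1728 + 0.0432)/0.8208 = -0.68.
- 40% response: probabilities are 0.3456, 0.1536 and 0.0256, so mean kappa = -(0.3456 + 0.0768 + 0.0085)/0.5248 = -0.82.

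The gap of 0.14 comes from response alone. The 60% and 40% are assumptions; the article gives only 50% overall. Response could differ by group, because Survey respondents describes programme-supplied contacts for Stepping Up counties and web searching for comparison counties.

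**B. Two rankings of m goals (primary measure)**

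The number of goals is not given; m = 4 to 12 is assumed. With M exact rank matches, unweighted kappa = (M/m - 1/m)/(1 - 1/m) = (M - 1)/(m - 1).

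| m = 8 | Unweighted kappa | Quadratic-weighted kappa = Spearman |
|---|---|---|
| One adjacent swap (M = 6) | 5/7 = 0.71 | 1 - 6×2/504 = 0.98 |
| All neighbouring pairs swapped (M = 0) | -1/7 = -0.14 | 1 - 6×8/504 = 0.90 |
| Full reversal (M = 0) | -1/7 = -0.14 | -1.00 |

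A single adjacent swap gives (m - 3)/(m - 1), which is 1/3 = 0.33 at m = 4 and 9/11 = 0.82 at m = 12. Over all orderings with Spearman at least 0.8, unweighted kappa is at or below 0 in 4.8%, 11.6% and 22.1% for m = 6, 7 and 8. Its mean there is 0.39, 0.31 and 0.24, against about -0.09 to -0.07 for orderings with Spearman at or below -0.8.

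**The case against.** **The type of kappa is left open, and an article may leave it to the full protocol or analysis plan.** This is fair for the rankings: a quadratic-weighted kappa fits the article's words and would be sound. It does not help the ratings, where weighting changes nothing with one item.

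**The two settings might be pooled as two items.** Kappa would then vary, but the definition treats the settings separately. The pooled version also behaves badly: jail ratings 9, 9, 9, 10 with community ratings 9, 9, 9, 9 give -0.143, and so do 1, 1, 1, 10 with 1, 1, 1, 1.

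**The chance term might be fixed or pooled across counties.** The index would then vary and unanimity would have a value. The article names no such form. The fixed version with 10 categories still ignores distance: 9, 9, 9, 10 and 1, 1, 1, 10 both give (0.5 - 0.1)/0.9 = 0.444, while their SDs are 0.50 and 4.50.

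**The reach is limited.** This stands. Performance monitoring is the primary mechanism. Common goals is secondary, and rating agreement is the secondary measure within it.

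A reader might also infer that the ranked-goals measure is equally empty, so that common goals cannot be tested at all. The documents do not support that. Unweighted kappa is not stated, and even that form keeps a single adjacent swap (0.33 to 0.82) well apart from a reversal and separates close from opposed lists on average.

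**Conclusion.** The secondary rating-agreement measure does not work as written. Under the usual kappas computed within a county, it takes a value fixed by the number of respondents (-1, -0.5 or -0.33 for Fleiss), or 0 for two-rater Cohen, and has no value for the counties that agree fully. It cannot show the planned difference in slopes or act as a mediator. This rests on two readings that the text supports: one item per setting, and a chance term taken from the county's own ratings.

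The ranked-goals measure needs a clarification only. If it were unweighted, some close lists would score exactly like a reversed one (-0.14 for both at an assumed 8 goals). That is a weakness for certain patterns, not a loss of all information. The primary common-goals test and the performance-monitoring analyses are not invalidated.

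**What to change.** **Ratings.** Replace the county kappa by the within-county mean absolute deviation or SD of the ratings, separately for jail and community, in counties with at least two respondents. Adjust for the number of respondents, since dispersion from two people is estimated differently from that of four. State that lower values mean closer agreement. Unanimous counties then score 0 instead of going missing.

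**Rankings.** State that the agency and county lists are compared by quadratic-weighted kappa, which equals Spearman's correlation for full rankings.

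**Cost.** Both changes rescore the same survey answers, with no new items or contacts. The small downside is that the rating measure is no longer a kappa, so its label in Table 3 and in the measure definition must change.

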##### System integration (agencies nested within counties)

 is a dichotomization of the NCJTP Relationship Assessment Inventory [38] total score (i.e., excluding the additional items). Counties with scores of 18 or more are considered to have achieved “system integration”. A secondary (county level) measure will reflect the degree to which each of 12 listed behavioral health screening and assessment instruments are used by and/or shared among multiple responding agencies within a county. For each of the 12 instruments listed, counties will receive a score (0 = no agencies use the same instrument, 1 = two agencies use the same instrument, 2 = three agencies use the same instrument, and 3 = all four agencies use the same instruments).

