### System integration

The CJ-IIM hypothesizes that implementation efforts will be most effective as they broaden engagement and ownership across agencies to develop a county-wide system of care, rather than adding single programs or trainings. Many agencies are involved in CJ behavioral healthcare (e.g., community mental health centers, substance use treatment agencies, police, courts, jail, probation, prison, and parole). Service linkage among them is often inadequate or non-existent [21, 22]. Previous analyses of CJ reform efforts suggest that the tendency is to implement a new program rather than working toward a cohesive system of care [23, 24]. The study will examine whether Stepping Up counties are more successful at creating integrated systems of care (mechanism) than are comparison counties, and whether doing so explains any observed differences in implementation outcomes.

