##### Secondary

We will conduct a series of analyses examining changes in interagency teams, common goals and missions, and integrated systems of care using scores from respective measures identified above, as mediators of a number of justice-involved individuals receiving services, number of EBPPs available, and number of resources using appropriate baseline measures or months since joining Stepping Up as controls.

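### The main system-integration measure is a cut-off on items that also make up the interagency-teams score, so these two secondary mechanism tests are not independent evidence

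*Protocol article*

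**What the plan says.** **Interagency teams** (Aim 1: Target mechanisms). For this scale the investigators write that "we integrated the NCJTP Relationship Assessment Inventory [38] with additional items based on the goals and priorities of Stepping Up". The result has 18 binary items, for example on sharing information about people who need treatment. It is scored "with one point assigned for each collaborative activity across the other 3 agencies", which gives a stated maximum of 54.

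**System integration** (same section). The main measure "is a dichotomization of the NCJTP Relationship Assessment Inventory [38] total score", and the article specifies that the added Stepping Up items are left out. The cut-off is 18 here and in Table 3. A measure labelled secondary, at county level, gives each of 12 screening and assessment instruments 0 to 3 points according to how many of the county's agencies use it in common.

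**Constructs.** The Background subsection on system integration describes broadening ownership across agencies to "develop a county-wide system of care, rather than adding single programs or trainings". The subsection on interagency teams describes agencies convening and functioning as a team. Table 1 lists the two as separate mechanisms.

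**Analysis.** Under Aim 1a, Secondary, each construct has its own hypothesis of faster improvement, and the shared-instrument measure has a separate comparison. The integration cut-off is given there as 6. Under Aim 1b, Secondary: "We will conduct a series of analyses examining changes in interagency teams, common goals and missions, and integrated systems of care", as mediators of the implementation outcomes.

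**The concern.** The article defines two different ideas: agencies working jointly, and a county-wide system in place of single programmes. On the main measures, the second idea has no content of its own. The integration indicator is a threshold on a sub-score that lies wholly inside the teams score.

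When the teams score rises through the original inventory items, counties cross the integration threshold as a consequence. If both slope tests favour Stepping Up, one set of answers will have supported two of the four mechanisms.

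The same holds for mediation. A score and a threshold on part of that score cannot show whether integration adds anything to joint activity, yet the Background says the study will examine whether integration explains differences in outcomes.

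**Working it through.** **Inputs from the article.** 18 binary items, 3 other agencies, maximum total 54; integration cut on the original items only, at 18 (Measures and Table 3) or 6 (Aim 1a). The number of original items, k, is not given.

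**The plan's own figure.** 18 items × 3 agencies × 1 point = 54, which reproduces the stated maximum.

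**Does the teams total determine integration status?** Assume the original items are scored across 3 agencies in the same way. The additional items then contribute up to 54 − 3k points. A non-integrated respondent has a sub-score of at most 17, so a total of at most 17 + 54 − 3k = 71 − 3k. An integrated respondent has a total of at least 18. Totals from 18 to 71 − 3k are therefore compatible with both states:

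| k (assumed) | Maximum sub-score, 3k | Totals compatible with both states |
|---|---|---|
| 6 | 18 | 18 to 53 |
| 9 | 27 | 18 to 44 |
| 12 | 36 | 18 to 35 |
| 15 | 45 | 18 to 26 |
| 17 | 51 | 18 to 20 |

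The total does not fully determine the indicator, so the two measures are nested but not identical.

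**How strong is the overlap?** A simulation drew 54 binary responses from a one-factor probit model, with each response endorsed 50% of the time and n = 40,000. Inter-item correlation is on the latent scale. Results at the cut-off of 18:

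| k | Inter-item correlation | r (total, sub-score) | r (total, indicator) | AUC of total for indicator |
|---|---|---|---|---|
| 9 | 0.2 | 0.95 | 0.71 | 0.974 |
| 9 | 0.4 | 0.98 | 0.79 | 0.988 |
| 12 | 0.2 | 0.97 | 0.80 | 0.984 |
| 12 | 0.4 | 0.99 | 0.84 | 0.994 |
| 15 | 0.2 | 0.99 | 0.76 | 0.994 |
| 15 | 0.4 | 1.00 | 0.82 | 0.998 |
| 17 | 0.2 | 1.00 | 0.72 | 0.998 |
| 17 | 0.4 | 1.00 | 0.80 | 0.999 |

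With uncorrelated items the AUC is 0.894 (k = 9) and 0.893 (k = 12), with correlations of 0.36 and 0.65. With k = 6 a score of 18 requires every item to be endorsed, and the indicator is almost always 0.

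**Analytic cross-check.** For a normal score cut at upper-tail proportion p, the correlation of the score with its own indicator is φ(z)/√(p(1 − p)). At p = 0.5 this is 0.399/0.500 = 0.798. At p = 0.25 it is 0.318/0.433 = 0.734. If the sub-score and the integrated total correlate 0.9 (assumed), these become 0.798 × 0.9 = 0.72 and 0.734 × 0.9 = 0.66. That is the same order as the simulation.

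**At the cut-off of 6.** For k = 9 to 17 and inter-item correlation 0.2 to 0.4, the indicator is positive in 83% to 99% of cases. The correlation with the total is then 0.25 to 0.64, while the AUC stays at 0.98 to 1.00. The choice of cut-off changes the correlation but not the nesting of the items.

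**The case against.** A reader might infer that integration is simply a cut-off on the 0 to 54 teams total, and that the study therefore cannot tell the two mechanisms apart. The article does not support either step. The cut is on the original inventory without the added items, and a range of teams totals is compatible with both states. The shared-instrument measure does not come from the inventory and has its own group comparison under Aim 1a. The reference under Aim 1b to the respective measures may include it. Table 3 lists it first under system integration and marks neither measure as primary.

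Two further objections stand. Both constructs are secondary in Aims 1a and 1b, and the primary mechanism, performance monitoring, is untouched. The overlap figures rest on an assumed item count and assumed item correlations, and they describe levels at one time, whereas the aims concern rates of change. Whether mediators are modelled jointly or one at a time is detail that the full analysis plan may hold.

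None of this removes the core. The article itself fixes the content of both main measures and gives each its own hypothesis and mediator test. Joint modelling would not give the integration indicator content of its own.

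**Conclusion.** The point holds in limited form. Every item behind the main integration indicator also enters the teams score, so results on these two measures share evidence and should not be read as support for two mechanisms. That conclusion follows from the definitions and needs no assumption.

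The size of the overlap does need assumptions. For 9 to 17 original items and inter-item correlations of 0.2 to 0.4, the correlation with the indicator at 18 is about 0.71 to 0.84. It is weaker if items are uncorrelated, and it cannot be fixed while the item count is unstated. The constructs can still be separated, but only through the secondary shared-instrument measure.

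The conflict between cut-offs of 18 and 6 is a separate defect. The two numbers differ by a factor of 3, the number of other agencies, but the article does not say that scaling is the reason.

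**What to change.** 1. Report the dichotomy as a descriptive summary of the interagency-teams inventory. Do not count it as a separate mechanism in Aim 1a or a separate mediator in Aim 1b.
2. Base any claim that system integration acts beyond teamwork on the shared-instrument score. Restrict it to counties with at least two respondents and scale it to the number responding. The raw score per instrument can reach only 1, 2 or 3 with two, three or four respondents, so dividing by respondents minus one puts counties on a common 0 to 1 scale.
3. State how many of the 18 items are original, and reconcile the cut-off in Measures and Table 3 with the one in Aim 1a.

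**Cost.** No new data are needed. The shared-instrument score covers a narrower part of integration, and it cannot be computed for counties with fewer than two respondents.

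The article's own figures bound that loss at one wave: 1900 respondents in 712 counties, at most 4 each. If x counties have exactly one respondent, then x + 4(712 − x) ≥ 1900, so x ≤ 948/3 = 316. At least 712 − 316 = 396 counties would have two or more. Attrition over later waves would lower this.

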#### Aim 2: implementation outcomes

##### Number of justice-involved adult clients receiving behavioral health services (agencies nested within counties; primary)

After defining “justice-involved” and asking whether each of the EBPP described below is available in the county, we ask respondents how many justice-involved individuals received any mental health service and how many received any substance use service in their agencies in the past year.

